#### Interrupted time series power calculation and analysis

The lack of estimates for some parameters required for the calculation of an ITS study sample precludes the calculation of a precise sample size. However, 36 points of observation (12 months before, 24 months after) should provide > 80% power to detect a significant effect of the intervention on primary outcome measures, assuming an effect size > 0.5 (medium effect or greater), autocorrelation > − 0.1, and a first-order autoregressive segmented regression model with both level (intercept) and trend (slope) changes expected [53]. To isolate the effect of the COMPAS+ QIC on the three quality indicators from other changes that could take place during the study period while adjusting for time, seasonal trends, and random errors, differences between the two study conditions (COMPAS+ or feedback only) will be assessed using linear mixed models for longitudinal data, where individuals’ data observed over time are nested into QICs to take account of the inter-QIC correlation. Descriptive statistics will also be generated for both study groups and all QICs.

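### The printed power above 80% cannot be reproduced for a medium standardised effect in the single 12 + 24-point segmented regression described; a 0.5 SD level change has about 10%

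*Protocol article*

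**What the plan says.** The section on interrupted time series power calculation and analysis opens with a disclaimer: "The lack of estimates for some parameters required for the calculation of an ITS study sample precludes the calculation of a precise sample size". It then gives a figure all the same. The design is "36 points of observation (12 months before, 24 months after" months, and this "should provide > 80% power to detect a significant effect of the intervention on primary outcome measures, assuming an effect size > 0.5 (medium effect".

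Three conditions are attached:
- effect size: "assuming an effect size > 0.5 (medium effect or greater";
- autocorrelation: "autocorrelation > − 0.1";
- model: "a first-order autoregressive segmented regression model with both level (intercept) and trend (slope) changes expected".

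A literature reference is cited. The article does not print the significance level, the SD that standardises the effect, the coefficient to which 0.5 applies, or any upper limit on autocorrelation. The same paragraph names a different analysis for comparing the two study conditions: a linear mixed model on individuals' data nested in the collaboratives.

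**The concern.** The number of points, their split, the model and the effect size are all printed, so the claim can be checked. On the scale where 0.5 is ordinarily called medium, a difference in SD units, 12 pre-intervention points fix the baseline trend poorly. A level change of half an SD is then smaller than its own standard error.

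The autocorrelation condition also looks reversed. A claim of at least 80% power needs a limit on the side where power is lost. Here the limit excludes only the more negative values, where power is higher.

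The sentence is the only quantitative support for the length and split of the observation window, and it is claimed for the primary outcome measures generally. A reader who relies on it may give a null result in such a series more weight against a medium effect than the design can bear.

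**Working it through.** **Inputs.** From the article: 12 pre and 24 post points, AR(1), intercept, trend, level change and slope change (36 - 4 = 32 residual df), effect 0.5. Assumed, because not printed: two-sided alpha 0.05; effect in SDs of the monthly series (marginal SD = 1); autocorrelation ρ treated as known.

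**Method.** With design matrix X = [1, t, post, post × time since interruption] and R having entries ρ^|i-j|, Var = (X'R⁻¹X)⁻¹. Power is P(F' > F₀.₉₅) with noncentrality λ = (effect/SE)² on 1 and 32 df, or the 2-df equivalent for a joint test.

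**Standard errors at ρ = 0, by hand.** The pre-period has mean time 6.5 and sum of squares 143; the post-period has 24.5 and 1150.
- Level change at t = 13 (time since interruption starts at 0): 1/12 + 6.5²/143 + 1/24 + 11.5²/1150 = 0.0833 + 0.2955 + 0.0417 + 0.1150 = 0.5355, so SE = 0.732.
- Level change at t = 12 (time since interruption starts at 1): 1/12 + 5.5²/143 + 1/24 + 12.5²/1150 = 0.4724, so SE = 0.687.
- Slope change: 1/143 + 1/1150 = 0.00786, so SE = 0.0887.

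**Attempt to reproduce the plan's figure.** For a 0.5 SD level change, 0.5/0.732 = 0.68 gives λ = 0.47 and power 10.2%; 0.5/0.687 = 0.73 gives λ = 0.53 and power 10.9%. Neither approaches 80%. Ranges below cover the two time codings.

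| Two-sided power, medium-effect readings | ρ = -0.1 | 0 | 0.4 | 0.5 |
|---|---|---|---|---|
| Level change 0.5 SD | 11.0-11.9% | 10.2-10.9% | 8.5-8.9% | 8.5-8.9% |
| Joint test, 0.5 SD plus a further 0.5 SD by month 24 | 9.1-9.6% | 8.5-8.9% | 7.3-7.5% | 7.3-7.5% |
| Before/after means, no trends (not the named model) | 32.5% | 28.0% | 16.5% | 14.9% |

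The mean-shift row at ρ = 0 uses SE = √(1/12 + 1/24) = 0.354, so λ = 2 on 34 df. A slope change reaching 0.5 SD at month 24 has under 6% from ρ = -0.1 upward. One-sided, the level test reaches 17.5% at ρ = 0. Simulation with ρ estimated gave rejection rates of 15-17% for the level change.

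**Readings that do exceed 80%.**
- A slope change of 0.5 SD per month: 0.5/0.0887 = 5.6 standard errors, power above 99% at ρ = 0. By month 24 the slope alone has moved the series 0.5 × 23 = 11.5 or 0.5 × 24 = 12 SD.
- Cohen's f = 0.5 on 1 df: λ = 36 × 0.25 = 9, power 82.9%. Reading 0.5 as f² also exceeds 80% (98.4% on 1 df). The conventional medium values on these scales are f = 0.25 (30.7%) and f² = 0.15 (61.6%).
- A one-sample t-test on all 36 points: 83.1%. This has no pre/post split and is not the named model.

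**Autocorrelation.** The table shows power falling as ρ rises from -0.1 to moderate positive values. More negative ρ raises it: level-change power is about 19-21% at -0.5, a value the condition excludes. On the per-month reading (0.5 on both level and monthly slope), joint power with the innovation SD drops to about 56% at 0.7 and 26% at 0.9, both allowed by the condition.

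**Detectable effects.** With 32 df, 80% power needs effect/SE = 2.889.
- ρ = 0: level 2.889 × 0.687 = 1.99 to 2.889 × 0.732 = 2.11 SD; slope 2.889 × 0.0887 = 0.26 SD per month.
- ρ = 0.4 (SE 0.838 to 0.887 for level, 0.1193 for slope): level 2.42 to 2.56 SD; slope 0.34 SD per month.

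**The case against.** The best defence is that the article never says what 0.5 is. It expects both level and trend changes, and if 0.5 applies to both coefficients, with trend measured per month, the joint test has more than 99% power near zero autocorrelation. With the marginal SD it stays above 80% at every autocorrelation tried from -0.1 to 0.9. The cited reference, which is not at hand, may define the scale in this way. This stands to the following extent: a reader might infer that no reading yields the printed power, and that would be too strong. But a shift of about 12 SD cannot be called medium, so the sentence needs correcting on that reading too.

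The disclaimer and the hedged verb also deserve weight. They explain why no exact sample size is given; they do not support a power threshold.

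A reader might also infer that power falls steadily with autocorrelation. It does not: with the marginal SD, level-change power is flat from 0.4 to 0.5 and recovers to 17.7-18.5% at 0.9, still far from 80%.

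Finally, a reader might infer that the trial would miss a medium effect nine times in ten. The article does not support this. The between-arm comparison is a mixed model on individual data, and the single-series calculation is not its power. Nor does the article say that a null result will be taken to exclude a medium effect.

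**Conclusion.** The concern holds for the printed figure. For a medium effect in SD units, the single series described has about 10% power for a level change and about 9% for the joint test at autocorrelation 0; even the simplest before/after contrast has 28%, or 32.5% at -0.1. The claim is met within the named model only on scales where 0.5 is not medium. The autocorrelation condition bounds the wrong side over the range from -0.1 to moderate positive values.

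These results rest on a two-sided alpha of 0.05, effects in marginal SDs of the monthly series and known autocorrelation. The exact level-change figures shift slightly with how time since interruption is coded. The conclusion concerns the power sentence and does not establish the power of the mixed-model comparison between the two arms.

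**What to change.** Revise the sentence as follows:

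1. Delete the claim of more than 80% power at an effect size of 0.5.
2. Define the effect size: which coefficient (level, monthly slope, or effect at a named month), which SD (marginal or innovation), and which alpha and sidedness.
3. State the detectable effect under those definitions. For example, under the assumptions used here, 80% power needs a level change of about 2.0 to 2.1 SD or a slope change of about 0.26 SD per month at autocorrelation 0, and about 2.4 to 2.6 SD or 0.34 SD per month at 0.4.
4. Give autocorrelation as a range with an upper limit that the sponsor can justify.
5. Say that the figure refers to a single segmented-regression series and not to the between-arm mixed-model comparison.

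The cost is one sentence and a short recalculation. No sites, patients or data are added. The stated figure becomes less favourable.

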### Qualitative component multiple case study

#### Setting and participants

The nine integrated health centres recruited to participate in the ITS study will also participate in the multiple case study. Baseline and longitudinal data will be collected to provide a rich description of each control and intervention site context and impacts of the received intervention. Between 7 to 10 key informants will be recruited for each site (senior managers and middle chronic disease and primary care managers) to participate in interviews. COMPAS+ workshops participants (managers, professionals, patients) and local implementation teams will also participate in the multiple case study.

### Data collection

#### Baseline assessment of control and intervention groups

Baseline interviews will be conducted for each case. The purpose of these interviews is to establish a portrait of the current organization of services and quality of care for people with the targeted chronic disease and to assess the extent to which QI and transformation projects have previously been implemented or are currently underway or planned in the region. This baseline evaluation will shed light on the adoption of best practices in chronic disease care by integrated health centres and their partners, help identify contextual factors at play in each region, and provide a basis for comparing services before and after the COMPAS+ QICs. Semi-structured individual and/or group interviews will be conducted with key informants (*n* = 7 to 10), including senior and middle managers responsible for chronic diseases and primary care services.

### Documenting implementation of QI projects

#### Control group

Following the feedback alone intervention, interviews will be conducted with the same key informants interviewed at baseline in each control site to document initiation of any QI projects or changes brought to services for the targeted chronic disease. Interviews will also capture the ways in which the feedback intervention supported or not the implementation of these projects or changes. Key informants will also be asked to share documents or reports that may be relevant to the QI projects.

#### Intervention group

To measure if COMPAS+ results in the initiation and implementation of QI projects, the local implementation committees will complete a project charter every four months. It will provide information on the content and level of implementation of QI projects. The tool developed by Lemire & Litvak [54] will be used, though Lean A3 reports [55] may be utilized as an alternative when already in use by the participants. During the follow-up phase of the QI project, local committee meetings will be recorded, and we will maintain a log (field notes) to continuously document the QI processes used by these committees. The level of achievement of the local QI projects will be assessed using Goal Attainment Scaling (GAS) [56] at 12 and 24 months after the intervention. GAS is an appropriate method to assess programs that have an individualized approach to intervention planning and was shown to be a reliable, valid and responsive method to document the impact of QI programs [57, 58]. GAS scales will be developed in collaboration with each local implementation committee. Any relevant documentation relevant to the QI projects will also be collected.

### Documenting secondary outcomes, levels of implementation and influencing factors for the intervention group

Data will be collected from individual health professionals and managers who participated in the COMPAS+ workshops to document the pre- and post-workshop levels of innovative culture (18 items) [59, 60], willingness and preparation for change (13 items) [60, 61], interprofessional collaboration (20 items) [62, 63], communication (5 items) [64], and readiness for patient engagement (5 items) [65]. These are validated scales that have been used in other studies evaluating QICs. They were pre-tested during the pilot phase of COMPAS+ and their scores revealed pre-intervention differences between sites. Data on these measures will be collected at the time of the workshops and at 12 and 24 months post-workshop through an online survey platform.

To document implementation levels and factors influencing implementation, field notes will be kept by the research team to document all meetings with the local implementation committees and interactions with local stakeholders, thus capturing vital information on QIC implementation and impacts throughout the course of the study. A structured grid will be used to track if the delivery of the three intervention phases went as planned and whether and how the support provided by the COMPAS+ team varied across sites.

Finally, group interviews, lasting one to three hours, with the local implementation teams of each large integrated healthcare organization will be conducted by a research assistant at 24 months of follow-up based on the Inquire Framework [36] to document the individual, team, organizational, and contextual factors that influence QI process.

#### Multiple case study data analysis

The framework method [66] will be used to analyse the qualitative and descriptive quantitative data collected for each integrated health centre and QIC. The advantage of this method is that it was developed for use in large-scale applied health research and is very useful to compare data across cases as well as within individual cases. It is composed of 7 stages: 1) transcription, 2) familiarisation with the interview, 3) coding, 4) developing a working analytical framework, 5) applying the analytical framework, 6) charting data into the framework matrix and 7) interpreting the data. In this approach, the coding aims to classify all the data so it can be compared systematically with other part of the data set. Inductive and deductive approaches (informed by the INQUIRE framework and COMPAS program theory) will be used. After coding a few cases, an analytical framework will be developed and apply to the other cases. Several iterations of the framework will be required. After applying the analytical framework to all the cases, a spreadsheet will be used to generate a matrix and the data will be charted into the matrix. Charting ensures paying close attention to each case before moving to interpretation and conduct cross-case analysis [66]. The analysis will ultimately allow us to produce narrative reports describing the story of each integrated health centre’s experience with the COMPAS+ or feedback interventions.

### Integration of the quantitative and qualitative study components

Based on the framework developed by Pluye and collaborators [67], a combination of two types of mixed methods analysis strategies will be used: comparison of QUAN and QUAL results obtained separately and assimilation of QUAN data into QUAL data. First, quantitative data collected for the ITS study will be added to the matrix and integrated in a single visual [40]. Multiple repeated quantitative baseline and follow-up data collected for the ITS will be compared to qualitative data collected during interviews to provide a thorough description of each study site. Convergence and divergence between qualitative and quantitative results will be assessed. Afterwards, quantitative data will be transformed into qualitative data to be analysed with the qualitative data. Based on the integration of both kinds of results, study sites will be categorized as high, moderate or low at implementing QI projects whether they are intervention or control sites. Characteristics and factors between cases will be identified and explanations for differences in the level of implementation, in the influence of contextual factors and possible interaction with achieved outcomes will be generated to provide clear answers to objectives 2 and 3 of this study. Two experienced qualitative researchers will conduct these analyses, in close collaboration with our patient partners and interdisciplinary research team that will meet regularly during the analyses phase.

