### Study objectives

The overall aim of this study is to evaluate implementation and impact of COMPAS+ QICs for chronic diseases prevention and management in primary care. The specific objectives are to:
Evaluate the extent to which COMPAS+ is more effective than feedback alone in improving the quality of care offered to people with chronic diseases, notably diabetes or COPD.Evaluate the extent to which COMPAS+ supports the implementation of QI projects, the improvement of interprofessional collaboration and the integration of a culture of continuous QI in primary care.Describe variations in the implementation of the COMPAS+ intervention and document the influence of contextual factors on the effects of the intervention.

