#### Outcomes measures

To assess the effectiveness of the COMPAS+ QICs, we will use three main measures of primary care quality easily retrievable from INESSS’s health administrative databases: [1] the number of emergency visits for ambulatory care sensitive conditions, a widely used measure of primary care accessibility and quality [46, 47], [2] number of patients visiting five or more different physicians over a period of twelve months, because it is an indicator of how formal the relationship between a family physician and a patient is (patient rostering has been recognized as an important feature of a high-performing primary care system) [48–50]; and [3] persistence to medication regimens over a period of twelve months, since poor adherence compromises effectiveness of treatment and health of patients at risk of chronic disease complications [51, 52].

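### The site implementation grade may draw on the ITS outcomes and is then related to achieved outcomes, so part of any implementation–outcome link is built in

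*Protocol article*

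**What the plan says.** The section Integration of the quantitative and qualitative study components (protocol article) sets out a sequence:

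- The ITS data enter the site matrix: "quantitative data collected for the ITS study will be added to the matrix and integrated in a single visual". Quantitative and qualitative results obtained separately are compared for agreement and disagreement.
- After that, "quantitative data will be transformed into qualitative data to be analysed with the qualitative data".
- The grade follows: "Based on the integration of both kinds of results, study sites will be categorized as high, moderate or low at implementing QI projects". Sites in both arms are graded.
- The last step generates explanations for differences in implementation level, for the influence of context, and for "possible interaction with achieved outcomes will be generated to provide clear answers to objectives 2 and 3 of this study".

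The section Outcomes measures says what the ITS data are: "To assess the effectiveness of the COMPAS+ QICs, we will use three main measures of primary care quality easily retrievable from INESSS’s health administrative databases". They are emergency visits for ambulatory care sensitive conditions, patients seeing five or more physicians in a year, and twelve-month medication persistence. Objective 3 reads: "Describe variations in the implementation of the COMPAS+ intervention and document the influence of contextual factors on the effects of the intervention".

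**The concern.** None of the three ITS outcomes measures whether a quality improvement (QI) project was carried out. They measure what such projects are meant to change. If they help decide which sites count as strong implementers, a site with good outcomes is more likely to be graded high partly because of those outcomes. Comparing grades with outcomes afterwards then partly compares the outcomes with themselves. No sentence keeps the outcomes out of the grade or the graders unaware of them.

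What is at stake is the statement that better-implementing sites did better, or did not. The article's Discussion expects the study to inform wider roll-out of the program, and this statement would be natural evidence for it. The problem needs no significance test: a narrative cross-case comparison takes on the same bias.

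**Working it through.** The article gives no figure for this step, so there is none to reproduce. The check is a reading of the text followed by an illustration.

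**1. What can feed the grade**

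| Source | Where described | Sites covered | Measures |
|---|---|---|---|
| ITS data | Outcomes measures; Integration section | all nine | effectiveness outcomes |
| Key-informant interviews and shared documents after feedback | Control group | three control sites | implementation |
| Project charters, Goal Attainment Scaling (GAS), project documents | Intervention group | six intervention sites | implementation |
| Field notes, delivery grid, 24-month group interviews | Documenting secondary outcomes, levels of implementation and influencing factors | six intervention sites | implementation and context |

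The grade rests on both kinds of results and covers both arms. The Integration section names one quantitative source, the ITS data. They are also the only follow-up quantitative data described for all nine sites. Outcome data can therefore enter the grade.

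**2. How the grade is used**

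The sentence after the grading step relates level of implementation to achieved outcomes. The same data can thus stand on both sides of the comparison.

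**3. Illustration of size**

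Assumptions, none of them from the article:
- true implementation I and outcome Y are independent standard normal variables, so there is no true link, and higher Y is better;
- there is one outcome (the article has three);
- the grading score is S = (1 − w)·I + w·Y, cut into equal thirds.

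Before the score is cut into grades, the correlation of S with Y is w / √(w² + (1 − w)²):
- w = 0.10: 0.10 / √(0.01 + 0.81) = 0.11
- w = 0.25: 0.25 / √(0.0625 + 0.5625) = 0.32
- w = 0.50: 0.50 / √(0.25 + 0.25) = 0.71

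Results for the three-level grade, from 40,000 simulated sets per row:

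| Sites | w | Mean correlation, grade with outcome | High minus low, mean outcome (SD) | High group better than low group |
|---|---|---|---|---|
| 9 | 0 | 0.00 | 0.00 | 49% |
| 9 | 0.10 | 0.09 | 0.22 | 61% |
| 9 | 0.25 | 0.27 | 0.63 | 79% |
| 9 | 0.50 | 0.61 | 1.41 | 98% |
| 6 | 0.10 | 0.09 | 0.21 | 58% |
| 6 | 0.25 | 0.26 | 0.60 | 73% |
| 6 | 0.50 | 0.60 | 1.35 | 95% |

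With w = 0, when the grade uses implementation evidence only, the spurious link disappears. Any positive weight creates one. It is small at 0.10 and large at 0.50.

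**The case against.** The other side has four arguments.

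- **The article does not say that ITS effects determine the grade.** The quality being graded is implementation of QI projects, and the plan has dedicated measures of that. The section Multiple case study data analysis refers to descriptive quantitative data in general, so the quantitative side could include goal attainment or survey scores. A condensed article may also leave grading criteria to the full protocol. This stands as far as the weight is concerned: it is unknown and could be small. It does not remove the point, because the article does state the basis and the order of grading, names the ITS data and excludes nothing.
- **Separately obtained results are compared first.** A site with good implementation and poor outcomes should show up as divergent before grading. This is a partial safeguard. It neither fixes the grade beforehand nor hides the outcomes from the graders, and grading comes after the data are merged.
- **The step is explanatory and qualitative.** No regression or test of outcome on grade is planned. This stands, and false-positive rates for such a test would describe an analysis that nobody proposes. The built-in direction of the comparison remains.
- **Much of objective 3 does not use the link.** This also stands. Variation in implementation and the role of context rest largely on interviews, field notes and the delivery grid.

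A reader might infer that the association is guaranteed, or that objective 3 cannot be answered. The documents support neither. The first depends on a weight they do not give, and the second overlooks the evidence that does not pass through the grade.

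**Conclusion.** The concern holds in a limited form. As written, outcome data can enter the implementation grade, and implementation level is then related to achieved outcomes. To the extent that the outcomes influence the grade, that link is partly built in. That part of the answers to objectives 2 and 3 cannot be interpreted cleanly.

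The descriptive and contextual parts of objective 3 are not affected. The randomised ITS comparison for objective 1 does not use the grade and is not affected either.

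The size cannot be fixed from the article. The simulated correlations, from about 0.09 to 0.61 for nine sites, show direction and a plausible range under an assumed weight, equal thirds and a single outcome. They do not estimate the bias in this study. The point rests on reading the quantitative results behind the grade as including the ITS data. That is the natural reading of the section, though not the only possible one.

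**What to change.** Revise the Integration section so that grading comes before the ITS results are added:

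1. The two qualitative researchers already planned assign the three-level grade from implementation evidence only, without seeing ITS results, and lock it.
2. The grade for all nine sites uses sources available in both arms, namely interviews and project documents. Goal attainment scores, charters, field notes and the delivery grid are described for the intervention group only. Using them in the all-site grade would judge the two arms on different evidence.
3. Those richer sources support a separate grade among the six intervention sites, locked in the same way.
4. ITS results are then added to the matrix and compared with the locked grades.

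No new data, sites or staff are needed. The cost is in sequencing and access: grading must be finished, and ITS results withheld from the graders, before integration meetings discuss outcomes. That takes some discipline, because the article has these researchers working closely with a team that meets regularly during analysis.
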